## Abstract

**Background:**

Constipation is common in adults and up to 20% of the population report this symptom. Chronic constipation (CC), usually defined as more than 6 months of symptoms, is less common but results in 0.5 million UK GP consultations per annum. The effect of symptoms on measured quality of life (QOL) is significant, and CC consumes significant health care resources. In the UK, it is estimated that 10% of district nursing time is spent on constipation. Trans-anal irrigation therapy has become a widely used treatment despite a lack of robust efficacy data to support its use. The long-term outcome of treatment is also unclear. A randomised comparison of two different methods of irrigation (high- and low-volume) will provide valuable evidence of superiority of one system over the other, as well as providing efficacy data for the treatment as a whole.

**Methods:**

Participants will be recruited based on predetermined eligibility criteria. Following informed consent, they will be randomised to either high-volume (HV) or low-volume (LV) irrigation and undergo standardised radiological and physiological investigations. Following training, they will commence home irrigation with the allocated device. Data will be collected at 1, 3, 6 and 12 months according to a standardised outcomes framework. The primary outcome is PAC-QOL, measured at 3 months. The study is powered to detect a 10% difference in outcome between systems at 3 months; this means that 300 patients will need to be recruited.

**Discussion:**

This study will be the first randomised comparison of two different methods of trans-anal irrigation. It will also be the largest prospective study of CC patients treated with irrigation. It will provide evidence for the effectiveness of irrigation in the treatment of CC, as well as the comparative effectiveness of the two methods. This will enable more cost-effective and evidence-based use of irrigation. Also, the results will be combined with the other studies in the CapaCiTY programme to generate an evidence-based treatment algorithm for CC in adults.

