## Trial objectives

### Primary objectives

To compare the impact upon patient disease-specific QOL of TAI initiated with a low-volume versus a high-volume system in patients with CC, measured at 3 months

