### Randomisation procedures

Patients will be randomised 1:1 into two groups; those who commence therapy with a low-volume device and those starting with a high-volume device. Patients will be stratified by sex and women by centre. Randomisation will be performed by a GCP-trained member of the research team using a bespoke, secure online system developed by the Pragmatic Clinical Trials Unit (PCTU).

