### Radio-physiological investigations (INVEST)

Patients will undergo standardised investigations. If INVEST previously conducted within the last 12 months, results can be carried forward. Pregnancy testing will be conducted as per routine NHS practice (10-day NHS rule) in respect to women between menarche and menopause. Women of equivocal status will have a pregnancy test performed as per routine care.Anorectal manometry using standard or high-resolution methods [39–41], depending on local availability, to determine defined abnormalities of recto-anal pressure gradient during simulated evacuation [42–44]Balloon sensory testing using standardised methods [45, 46] (2 ml air per second to maximum 360 ml) to determine volume inflated to first constant sensation, defaecatory desire and maximum tolerated volumes. Rectal hyposensation and hypersensation, defined in accord to gender-specific normative data on 91 healthy adults [47]. The recto-anal inhibitory reflex (RAIR) will also be elicited by a 50-ml rapid inflation (if necessary in 50-ml aliquots up to 150 ml)Fixed volume (50 ml) water-filled rectal balloon expulsion test [42, 43, 48, 49] in the seated position on a commode. Abnormal expulsion is defined as abnormal if failure to expel with a 1-min effort for men and 1.5 min for women [50]Whole gut transit study using serial (different shaped) radio-opaque markers over 3 days with a single plain radiograph at 120 h [51, 52]

Note: INVEST procedures conducted prior to recruitment to the study (i.e. within the past 12 months) may be done using locally available devices and methods.

All patients will undergo TAI therapy irrespective of INVEST results, and will be followed up in the same way. The purpose of INVEST in this study is to identify whether certain radio-physiological results correlate with treatment response, i.e. can we predict likelihood of benefitting from irrigation based on pretreatment investigations. Balloon sensory testing in combination with patient-reported urge to defaecate will be analysed as covariates to determine whether such a relationship is present.

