It is recognised that the study design has several limitations. From a methodological perspective, the fact that neither participant nor assessor blinding was feasible (due to the nature of the treatment and the nature of the outcome data being collected), leads to the possibility of performance bias and reporting bias, as both participants and assessors will (consciously or unconsciously) have particular preconceived ideas about the likely efficacy of each system. Attempts have been made, from a methodological and operational perspective, to limit the impact of this. The fact that every patient receives treatment is important, as it is a reasonable assumption that the placebo effect for each system is similar, thereby meaning that any observed difference between systems is a genuine one. Additionally, the option of switching systems after 3 months is designed to allow participants who have not had success with their original system to try the other one. This means that patients do not spend too long on ineffective treatment, and also allows longer-term data (more than 3 months) to evaluate the effectiveness of the treatment as a whole in the long term.

As can be seen from the ‘Trial status’ section below, recruitment nationally has fallen below the planned rate of recruitment. Several reasons for low recruitment have been identified through discussions with participating sites; these are mainly the result of variation in local practice (making the protocol difficult to implement), as well as service pressures and the pressure on research teams from doing more than one study in the CapaCiTY programme. This highlights the difficulties in implementing multisite studies, and even though attempts were made before study commencement to ensure sufficient flexibility in the proposed study design, problems have nonetheless been encountered.

Since recruitment has opened, recruitment rates at each study site are monitored and monthly meetings are held to discuss progress and to identify problems at an early stage. Teleconferences have been held with recruiting sites in order to discuss and resolve barriers to recruitment.

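### Every patient irrigates, so whole-cohort change is uncontrolled: the trial cannot supply controlled evidence that irrigation itself works, or show which tests predict benefit from it

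*Protocol article*

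**What the plan says.** The design is a two-arm comparison of irrigation systems. Under Randomisation procedures: "Patients will be randomised 1:1 into two groups", one starting with a low-volume and the other with a high-volume device. Under Radio-physiological investigations (INVEST): "All patients will undergo TAI therapy irrespective of INVEST results". The primary objective compares "TAI initiated with a low-volume versus a high-volume system in patients with CC, measured at 3 months". Trial design: rationale adds that after 3 months, when patients may change device, the comparison is between starting strategies. No unirrigated, delayed-start or external comparator is named.

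The article also makes claims about irrigation as such:

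- Abstract, Background: "as well as providing efficacy data for the treatment as a whole".
- Abstract, Discussion: "It will provide evidence for the effectiveness of irrigation in the treatment of CC", stated in addition to comparative effectiveness.
- Main Discussion, on what longer follow-up allows: "to evaluate the effectiveness of the treatment as a whole in the long term".
- INVEST section, on the purpose of the tests: "can we predict likelihood of benefitting from irrigation based on pretreatment investigations".

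The limitations paragraph in the main Discussion deals with lack of blinding. It treats the fact that all patients are treated as helpful, because the placebo effect can be assumed similar in the two systems. It does not mention the absence of a control without irrigation.

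**The concern.** The article justifies the trial partly by the lack of robust efficacy data for irrigation. A before-after change on an unblinded self-report scale, in a cohort where everyone is treated, does not fill that gap. It mixes any effect of irrigation with everything else that changes after enrolment.

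The prediction claim has the same weakness. To learn who benefits from irrigation, one must know how patients with a given test result would have fared without it, and no patient supplies that information.

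The results have uses beyond the trial. The Abstract says they will contribute to a treatment algorithm. Trial design: rationale says findings from both arms, separately and together, will be used to model the net value of irrigation to patients. If uncontrolled change were read there as a treatment effect, or prognostic factors as selection criteria, effectiveness could be misjudged and patients poorly selected.

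**Working it through.** **1. The plan's own figure.** Sample size section: difference 0.4, SD 1, 90% power, 5% significance (taken as two-sided). n per arm = 2 × (1.96 + 1.2816)² × 1² / 0.4² = 131.3, so 132; the t-test version gives 132.3, so 133. Total 266. Allowing for 10% loss, 266 / 0.9 = 295.6, so 296, which the plan rounds to 300. Power at 133 per arm is 90.4%. The figure reproduces, and it concerns only the difference between systems.

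**2. What randomisation identifies.**

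| Question | Randomised contrast? |
|---|---|
| High- versus low-volume, PAC-QOL at 3 months | Yes |
| High-first versus low-first strategy after 3 months | Yes |
| Which baseline factors favour one system over the other | Yes, through baseline-by-system interactions |
| Effect of irrigation as a whole | No: no patient goes without it |
| Which tests predict benefit from irrigation itself | No: same reason |

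**3. What else can move the whole-cohort score.**

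- Placebo response. The equal-placebo assumption removes it from the difference between arms. It stays in full in the pooled change.
- Natural course. Baseline PAC-QOL is taken at visit 1, and up to 8 weeks are tolerated for INVEST, so baseline can precede irrigation by weeks.
- Regression to the mean. Patients enter with self-reported problematic symptoms after failed treatment. There is no PAC-QOL entry threshold and symptoms are long-standing, so some regression is possible, but its size cannot be derived.
- Co-medication. Rescue laxatives are permitted, and other drugs too if symptoms are severe (Study interventions; Visit 2). The restriction on other therapies is stated only for the first 3 months.

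**4. Why a significant before-after change would not settle it (illustration).** Assumptions: 266 patients, no effect of irrigation, SD of change 1. Probability of p<0.05 in the direction of improvement = Φ(drift × √266 − 1.96), with √266 = 16.31.

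| Drift not due to irrigation | Probability of p<0.05 |
|---|---|
| 0.1 | 37% |
| 0.2 | 90% |
| 0.3 | 99.8% |

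The drifts are hypothetical. The table shows only that a small one would be declared significant.

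**5. The moderator question that the design can address.** The Clinical outcomes section allows at most three interactions between treatment and baseline characteristics. For a binary factor with prevalence f, N = 266 and SD 1 (assumed, with no gain from baseline adjustment), the standard error of the interaction is √(4/(Nf) + 4/(N(1−f))).

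| Prevalence | SE | Power for an interaction of 0.4 | Interaction detectable with 90% power |
|---|---|---|---|
| 50% | 0.245 | 37% | 0.80 |
| 30% | 0.268 | 32% | 0.87 |
| 20% | 0.307 | 26% | 0.99 |

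These interactions are valid randomised contrasts, but they inform choice of system only, and power for them is limited.

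**The case against.** The article promises to provide evidence and data, not proof, and it describes itself as a large prospective cohort as well as a trial. The primary objective, sample size and primary model concern only the two systems. The change to a strategy comparison after 3 months is stated openly. No before-after efficacy test is specified. Co-treatment is to be recorded for use as covariates, and interactions are to be fixed in advance in the SAP. The INVEST section also speaks of correlation with treatment response, which is a prognostic question loosely worded. All of this stands, and it makes the problem one of claims rather than of design. It does not remove the claims, which appear in the abstract and the discussion with no caveat about the missing control. Covariate adjustment for co-medication does not supply the outcome without irrigation.

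A reader might infer more than the document supports:

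- *That the trial can answer nothing but high versus low volume.* Continuation, acceptability, adverse events and costs on irrigation can be described validly. For example, a continuation of 50% among 266 patients would have a 95% interval of ±1.96 × √(0.25/266), about ±6 percentage points.
- *That the design inflates the change by a known amount.* No size for regression to the mean follows from the text. Nurse training is part of the intervention, not a co-treatment. Regulating laxatives could move scores either way.
- *That the algorithm or net-value model will take the PAC-QOL gain as a treatment effect.* The article does not state the model inputs. The net-value passage refers to persistence of benefit.

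**Conclusion.** The point holds as a matter of what the trial may conclude. The statements about the efficacy or effectiveness of irrigation as a whole, and about predicting benefit from it, attribute to the design a property it lacks. This follows from the allocation alone and needs no numerical assumption. The bias in whole-cohort change cannot be sized, or even signed with certainty, from the document. The 90% figure for a 0.2-point drift is an illustration that rests on an assumed SD of change of 1. The randomised comparison of systems and its sample size are unaffected.

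**What to change.** - **Abstract (Background, Discussion) and main Discussion:** limit causal conclusions to high- versus low-volume at 3 months and high-first versus low-first strategy thereafter. Describe whole-cohort PAC-QOL change as uncontrolled, and report it beside the co-medication data already collected. Keep continuation, acceptability, safety and cost as descriptive results.
- **Limitations paragraph:** state that there is no control without irrigation, and that the equal-placebo argument protects only the difference between systems.
- **INVEST and Clinical outcomes sections:** call baseline main effects prognostic for outcome on irrigation. Reserve claims of differential benefit for the pre-specified baseline-by-system interactions, and say that they guide choice of system only.
- **Net-value model and treatment algorithm:** if uncontrolled change is an input, label it as such and vary it in sensitivity analysis rather than entering it as a treatment effect.

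The cost is wording, a sensitivity analysis where the model uses such data, and a weaker headline claim. No patients, visits or procedures change.

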**Trial registration:**

ISRCTN, identifier: ISRCTN11093872. Registered on 11 November 2015. Trial not retrospectively registered. Protocol version 3 (22 January 2016).

**Electronic supplementary material:**

The online version of this article (doi:10.1186/s13063-017-1882-y) contains supplementary material, which is available to authorized users.

## Background

### Burden of disease

Constipation is common in adults and up to 20% of the population report this symptom depending on the definitions used [1–3], with a higher prevalence in women [1, 4, 5] and older people [6, 7]. Chronic constipation (CC), usually defined as more than 6 months of symptoms, is less common [8] but results in 0.5 million UK GP consultations per annum. A proportion of the population suffer symptoms which are both chronic and more disabling (about 1–2% of the population) [9]. Such patients, who are predominantly female [10], are usually referred to secondary care with many progressing to tertiary specialist investigation. Patient dissatisfaction is high in this group; nearly 80% feel that laxative therapy is unsatisfactory [11] and the effect of symptoms on measured quality of life (QOL) is significant [12]. CC consumes significant health care resources. In the US in 2012, a primary complaint of constipation was responsible for 3.2 million physician visits [13] resulting in (direct and indirect) costs of US$1.7 billion. In the UK, it is estimated that 10% of district nursing time is spent on constipation [14] and the annual spend on laxatives exceeds £80 million, with 17.4 million prescriptions being issued in 2012 (Health and Social Care Information Centre, 2013) [15].

### Pathophysiological basis of chronic constipation

The act of defaecation is dependent on the coordinated functions of the colon, rectum and anus. Considering the complexity of neuromuscular (sensory and motor) functions required to achieve planned, conscious and effective defaecation [16] it is no surprise that disturbances to perceived ‘normal’ function occur commonly at all stages of life. Clinically, such problems commonly lead to symptoms of obstructed defaecation, e.g. straining; incomplete, unsuccessful or painful evacuation; bowel infrequency; abdominal pain and bloating. After exclusion of a multitude of secondary causes (obstructing colonic lesions, neurological, metabolic and endocrine disorders), the pathophysiology of CC can broadly be divided into problems of colonic contractile activity and thus stool transit and problems of the pelvic floor. Thus, with specialist physiological testing (using a standard panel of radio-physiological tests of colonic and anorectal function, hereafter referred to as INVEST in this protocol), patients may be divided into those who have slow colonic transit, evacuation disorder, both or neither (no abnormality found with current tests). Evacuation disorders can be then subdivided into those in which a structurally significant pelvic floor abnormality is evident, e.g. rectocoele or internal prolapse (intussusception) and those in which there is a dynamic failure of evacuation without structural abnormality: most commonly termed ‘functional defaecation disorder (FDD)’.

### Chronic constipation management overview

Management of CC is a major problem due to its high prevalence and lack of widespread specialist expertise. In general, a step-wise approach is undertaken, with first-line conservative treatment, such as lifestyle advice and laxatives (primary care), followed by nurse-led bowel retraining programmes, sometimes including focussed biofeedback and psychosocial support (secondary/tertiary care). Although these treatments may improve symptoms in more than half of patients, they are very poorly standardised in the UK and are not universally successful [17]. Thus, patients with intractable symptoms and impaired QOL may be offered a range of costly, irreversible surgical interventions with unpredictable results [18, 19], sometimes resulting in major adverse events (AEs) or a permanent stoma.

### Overall rationale for the CapaCiTY programme

The current trial forms part of an NIHR-funded programme (PGfAR: RP-PG-0612-20001). This programme aims to develop the evidence base for the management of CC in adults which is currently lacking. This is in contrast to the management of CC in children for which NICE guidance has been recently published (http://pathways.nice.org.uk/pathways/constipation/clinical-management-of-idiopathic-constipation-in-children-and-young-people) [20, 21]; and for adults with faecal incontinence (http://pathways.nice.org.uk/pathways/faecal-incontinence). Thus, the current situation is one where there are considerable variations in practice, particularly in specialist services. With a number of new drugs gaining or seeking NHS approval [22–25] and technologies at a horizon-scanning stage [18, 26, 27] it is timely that the currently limited evidence base for adult CC is developed for resource-constrained NHS providers to have confidence that new and sometimes expensive investigations and therapies are appropriate and cost-effective. A cost-conscious pathway of care may help to reduce health care expenditure by appropriately sequencing the care provided, while targeting more expensive therapies at those most likely to benefit. Such data will inform the development and commissioning of integrated care pathways. An overview of the CapaCiTY programme is provided as a scheme (See Additional file 1) and includes a series of interlinked work package signature pages (WPs) that answer the important questions for patient care. A rolling programme of national recruitment will provide a large cohort of well-defined patients for subsequent studies within sequential WPs over 5 years. The focus will be on generating real-life evidence from pragmatic studies which will provide valid clinical outcome measures, patient acceptability and cost. Armed with such data it will be possible to develop an NHS management algorithm for CC which will meet patient, clinician and policy aims.

### Specific clinical background to the prospective cohort study of trans-anal irrigation (TAI)

Anal irrigation, using a variety of commercially available devices, has been rapidly disseminated internationally over the past 3–5 years, first in patients with neurological injury [28, 29] and subsequently in other CC groups [30, 31]. Despite a lack of published data other than from small selected case series, it is now available on the drug tariff and generally considered to be the next step in patients failing other nurse-led interventions such as biofeedback. Anal irrigation has permeated the UK market without robust efficacy data and with on-going concerns regarding longevity of treatment and complications [28, 32]. Retrospective clinical audit data and review [32] suggest a continued response rate after 1 year of approximately 50% with such patients, thus avoiding or delaying surgical intervention. An accurate assessment of response rate and acceptability of this intervention requires confirmation in a large prospective cohort, together with clinico-physiological predictors of success. In addition, two alternative systems for delivery of TAI exist; low-volume systems delivering approximately 70 ml per irrigation, and high-volume systems delivering up to 2 L of irrigation (although typically only 0.5–1.5 L is required per irrigation). The low-volume system is cheaper, costing approximately £750 p.a. based on alternate-day use, compared with approximately £1400–1900 for high-volume irrigation, and may be more acceptable to patients, and so a randomised study comparing the two systems is needed.

### Trial design: rationale

Robust data for the use of TAI therapy in chronic (idiopathic) constipation are lacking. In addition, there are no data demonstrating superiority of high-volume irrigation over low-volume systems. Given the differences in cost between the two systems, a randomised study of well-characterised patients comparing the two methods would provide useful information on whether one system holds a clear advantage over the other. Also, the short- and long-term efficacy and acceptability of therapy in CC could be evaluated. This is timely and informative given the rapidly increasing popularity of this treatment and the fact that TAI is an invasive therapy for which patient selection should also be optimised to maximise benefit.

In practice, patients will use one system only (plus defined ‘rescue therapies’ – see below) for a minimum of 3 months. After this time point they may switch to the other system if their initial therapy was ineffective/unsatisfactory. Thus, consenting patients will be randomised to initiate therapy with one of these systems but will have the option of switching to the other after an initial 3-month period. This allows us to identify response rates to each system in the short term (3 months), and thereafter this study is a comparison between treatment strategies (low-volume initiated therapy versus high-volume initiated therapy) rather than a pure comparison of the two techniques. This is a patient-centred study design aiming to limit the time that patients spend using ineffective therapy without being allowed to try an alternative. This also allows estimation of comparative cost-effectiveness of the two treatment pathways, and whether one system works better depending on the radio-physiological profile of the patient. Recent data estimates that approximately 85% of patients are still using irrigation at 1 month; this represents a significant short-term treatment failure rate [33]. Once patients have switched therapy, they may not switch back to the first system; once they have tried both systems and discontinued them then they will be considered to have completed the intervention and they will return to routine clinical care.

Irrigation is a maintenance therapy rather than a cure. In addition to outcome measures of the Patient Assessment of Constipation Quality of Life questionnaire (PAC-QOL) [34, 35] score at 3 months, patients will provide survival data (time until cessation of irrigation therapy due to lack of benefit). Switching systems does not affect this; the survival data is based on the use of irrigation irrespective of system. A survival analysis is appropriate since anal irrigation is time-consuming and inconvenient as a therapy and patients may find the process distasteful. Patients are unlikely to continue with treatment if they are not gaining worthwhile benefit from it; treatment continuation is a useful patient-centric assessment.

Consideration of the findings from both groups (individually and together) will be used to model the net value to patients of anal irrigation, considering persistence of benefit.

